#### Justification

2.5.4

The patient sample size was determined through a power analysis to ensure ≥80% statistical power for detecting a clinically meaningful improvement (ΔAUC more than 0.15) in diagnostic accuracy, aligning with FDA guidelines for validating AI-driven medical devices (36).

### Assignment of interventions

2.6

#### Randomization and allocation

2.6.1

A computer-generated randomization sequence will be created using the blockrand package in R, stratified by hospital tier (urban vs. rural) and clinician experience level (resident, attending, or chief physician). This approach ensures balanced allocation across subgroups, minimizing confounding effects from institutional resources or practitioner expertise. Participants will be assigned to either the control group (standard clinical diagnosis) or the model-assisted group (AI-supported diagnosis) at a 1:1 allocation ratio. The randomization sequence will be concealed in sequentially numbered, opaque envelopes managed by an independent statistician to prevent selection bias, ensuring equitable distribution of participants and maintaining trial integrity.

To ensure unbiased group assignment, an independent statistician uninvolved in recruitment or data analysis will prepare opaque, sequentially numbered envelopes containing group allocations (control or model-assisted). These sealed envelopes will be securely stored and only opened sequentially by a dedicated study coordinator after clinicians complete baseline assessments. This procedure rigorously prevents selection bias by concealing allocation details until the point of intervention assignment, thereby safeguarding the randomization integrity and ensuring equitable distribution of participants across study groups.

#### Blinding (masking)

2.6.2

To minimize bias, a single-blind design will be implemented for clinicians: those in the control group will remain unaware of their allocation status and the existence of the AI model, while clinicians in the model-assisted group will access predictions through a neutral interface labeled as a “Decision Support Tool,” avoiding explicit references to AI. Patients will be fully blinded to group assignments, with informed consent documents describing participation in “a study to improve influenza diagnosis” without disclosing AI involvement. Independent outcome adjudicators assessing severe influenza outcomes will also remain blinded to group allocations and model outputs, ensuring objective evaluation of clinical endpoints. This multi-layered blinding strategy safeguards against performance and detection bias, maintaining the trial’s scientific rigor.

#### Intervention groups

2.6.3

In the control group, clinicians (without any AI assistance) will diagnose influenza cases using standard clinical protocols, integrating symptoms, laboratory results, and imaging findings. Patients in this group will receive routine care based solely on clinician assessments.

In contrast, the model-assisted group will utilize a secure digital dashboard providing real-time AI predictions, including a risk score (0–100%) for severe influenza progression and highlighted contributing factors (such as prolonged fever duration, abnormal lymphocyte counts).

While the model offers data-driven insights, its outputs are non-prescriptive; clinicians retain full authority to accept, modify, or reject recommendations, ensuring clinical judgment remains central to decision-making. This design balances technological support with practitioner autonomy, reflecting real-world diagnostic workflows.

### Data collection

2.7

#### Data sources and tools

2.7.1

The study spanned 5 years. A significant amount of data collection relied on EHRs and patient self-report diaries (Table 2). Two modes of sampling and supplementation were set up. [name] would randomly sample 5% of the data every month to check for completeness. Patients can supplement their data submissions through the WeChat app.

#### Data collection timeline

2.7.2

The study’s data collection is structured into two distinct phases: retrospective (Phases I–II) and prospective (Phases III–V).

During the retrospective phase, EHRs data spanning 2019 to 2024 will be extracted from all 87 participating hospitals via institution-specific application programming interfaces (APIs), with completion targeted within 6 months to ensure timely progression to subsequent stages.

In the prospective phase, real-time data collection will occur throughout the 2025 influenza season, capturing clinical, diagnostic, and outcome variables as they emerge. These data will be synchronized daily to a centralized, secure database to maintain continuity and enable immediate analysis.

This phased approach balances historical insights with dynamic, real-world validation, ensuring comprehensive evaluation of the AI model across diverse temporal and operational contexts.

#### Quality control measures

2.7.3

To ensure data accuracy and consistency, comprehensive quality control protocols were implemented. Standardized training was provided to clinicians and data entry staff, focusing on EHR documentation practices (such as symptom coding conventions and structured data entry). Automated validation rules were applied to detect anomalies, including range checks (such as body temperature less than 42°C) and logical consistency validations (such as ensuring symptom onset dates precede diagnosis dates). Additionally, manual audits were conducted by independent reviewers, who cross-validated 10% of randomly selected records against source documents (such as laboratory reports, imaging files) to verify data fidelity. These layered measures (combining education, technology, and human oversight) minimize errors and enhance the reliability of the dataset for robust model validation.

#### Missing data handling

2.7.4

To minimize missing data, mandatory fields (such as viral subtype, symptom onset date) are enforced in digital entry forms, ensuring critical variables are consistently documented. For remaining missing values, multiple imputation via chained equations (MICE package) will be applied to continuous variables, leveraging iterative regression models to estimate plausible values under missing-at-random assumptions. Categorical variables with less than 10% missingness will undergo mode imputation, replacing gaps with the most frequent category, while variables exceeding this threshold will be excluded to avoid bias from unreliable estimations. This tiered approach balances data completeness with methodological rigor, preserving statistical validity while addressing real-world data imperfections.

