#### Subgroup analyses

2.4.3

Predefined subgroup analyses will assess heterogeneity in model performance across key variables to evaluate the impact of local healthcare infrastructure and influenza epidemiology.

patient characteristics: age (infants, children, adults, older adults), comorbidities (cardiovascular disease, diabetes), and vaccination status (yes, no);clinician factors: experience level (resident, attending, chief physician);hospital resource tier: urban or rural facilities;geographic variation: northern or southern regions of Jiangsu Province.

These analyses aim to identify subgroups where the model excels or underperforms, informing targeted clinical deployment. Statistical adjustments, such as Bonferroni correction for multiple comparisons and multivariable regression for confounders, will ensure robust interpretation of subgroup differences.

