#### Handling missing data

2.4.4

To address missing data, variables with more than 20% missing values will be excluded to ensure reliability. For remaining gaps, the Multivariate Imputation by Chained Equations (MICE) package in R will be employed, leveraging iterative modeling across variables to impute missing values under the missing-at-random assumption. This method preserves dataset integrity by estimating missing entries based on observed patterns, thereby minimizing bias while maintaining statistical power.

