#### Missing data handling

2.8.4

To address missing data, variables with more than 20% missing values (such as incomplete vaccination records) will be excluded to maintain analytical reliability. For remaining gaps, multiple imputation via chained equations (MICE package in R) will generate 10 imputed datasets for continuous variables, preserving statistical power under missing-at-random assumptions. Categorical variables with less than 10% missingness will undergo mode imputation, replacing missing entries with the most frequent category, while those exceeding this threshold will be excluded to avoid biased estimations. This protocol balances data completeness with methodological rigor, minimizing potential distortions in model performance evaluation.

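### Section 2.4.4 contradicts sections 2.7.4 and 2.8.4 on how missing categorical variables are handled, and the mode fill in the latter two is a poor choice

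*Protocol article*

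**What the plan says.** The protocol article sets out missing-data handling three times.

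- **Section 2.4.4 (Outcomes):** "variables with more than 20% missing values will be excluded to ensure reliability". Then, with no distinction by variable type, "For remaining gaps, the Multivariate Imputation by Chained Equations (MICE) package in R will be employed".
- **Section 2.7.4 (Data collection):** "multiple imputation via chained equations (MICE package) will be applied to continuous variables". For categorical variables: "Categorical variables with less than 10% missingness will undergo mode imputation, replacing gaps with the most frequent category". Those with more than 10% missing are dropped.
- **Section 2.8.4 (Statistical analysis):** "variables with more than 20% missing values (such as incomplete vaccination records) will be excluded to maintain analytical reliability". MICE "will generate 10 imputed datasets for continuous variables". The 10% rule for categorical variables is then repeated in substance.

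All three sections justify MICE by a missing-at-random assumption. Sections 2.4.3 and 2.8.3 pre-define vaccination status as a patient-level subgroup, and section 2.4.3 gives its levels as yes and no. Section 2.8.5 plans two sensitivity checks: a complete-case comparison, and the variation in AUC across imputed datasets.

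**The concern.** The three sections cannot all be followed for a categorical variable, and nothing says which prevails. The choice would be made once the missingness is known, and it decides which predictors enter the model and in what form.

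The categorical rule in 2.7.4 and 2.8.4 is also weak in itself. Filling with the mode is a single deterministic step that ignores both covariates and outcome. It is not valid under the missing-at-random assumption that the same sections invoke for MICE, and it carries no imputation uncertainty. Because the fill is identical in all 10 imputed datasets, the AUC-variation check cannot detect that uncertainty.

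The vaccination question is separate. A variable that the protocol gives as an example for exclusion is also one by which it promises to report results, and no fallback is stated.

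**Working it through.** **1. The rules side by side.** The documents give no missingness rates, so each rule is applied at illustrative levels.

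| Variable and % missing | 2.4.4 | 2.7.4 | 2.8.4 |
|---|---|---|---|
| Categorical, 5% or 9% | MICE | mode fill | mode fill |
| Categorical, exactly 10% | MICE | not stated | not stated |
| Categorical, 15% | MICE | excluded | excluded |
| Categorical, 25% | excluded | excluded | excluded |
| Continuous, 5% to 15% | MICE | MICE | MICE, 10 datasets |
| Continuous, 25% | excluded | MICE, no limit stated | excluded |

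The conflict covers categorical variables with up to 20% missing. Below 10% it concerns the method; between 10% and 20% it concerns whether the variable is kept at all. For continuous variables, 2.4.4 and 2.8.4 agree.

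**2. Distortion of a predictor's association by mode filling.** The plan has no figure of its own to reproduce. Assumptions, none from the documents: a binary predictor with prevalence q0 = 0.4 in non-severe cases, true odds ratio (OR) 2, and 10% severe cases.

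- Prevalence in severe cases: odds = (0.4/0.6) × 2 = 1.333, so q1 = 1.333/2.333 = 0.571.
- The more common observed class is predictor absent, so every gap is filled with absent.
- With fractions m1 (severe) and m0 (non-severe) missing, the filled prevalences are a = q1(1 − m1) and b = q0(1 − m0).
- OR after filling = [a/(1 − a)] / [b/(1 − b)].

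| m1 severe | m0 non-severe | Overall missing | a | b | OR after fill |
|---|---|---|---|---|---|
| 9.9% | 9.9% | 9.9% | 0.515 | 0.360 | 1.061/0.563 = 1.88 |
| 10% | 2% | 0.1×10 + 0.9×2 = 2.8% | 0.514 | 0.392 | 1.059/0.645 = 1.64 |
| 2% | 10% | 0.1×2 + 0.9×10 = 9.2% | 0.560 | 0.360 | 1.273/0.5625 = 2.26 |
| 30% (extreme) | 7% | 0.1×30 + 0.9×7 = 9.3% | 0.400 | 0.372 | 0.667/0.592 = 1.13 |

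Every row lies under the 10% threshold, so each would be mode-filled. Over true ORs of 0.5, 2 and 3, prevalences of 0.2 to 0.6 and 5% to 9.9% missing, missingness unrelated to outcome shrinks the log OR by about 1% to 11%. Outcome-related missingness can move it either way and by more.

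**3. Effect on AUC.** This is an indicative simulation with four binary predictors (log OR 1.0 each, prevalence 0.30 or 0.45), three continuous predictors, roughly 10% to 15% severe and split-sample AUC. With 9% missing completely at random in all four binary predictors, mode fill lowered AUC from 0.836 to 0.828 (prevalence 0.30) and from 0.833 to 0.821 (prevalence 0.45), a loss of 0.008 to 0.012. A random-draw fill lost about as much (0.826 and 0.821). With outcome-related missingness (10% against 2%) the shift was about 0.01 to 0.03 in either direction.

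**4. Vaccination status.** The example sits in the 20% clause of 2.8.4, and 2.4.4 has the same 20% limit. Above 20% missing, the variable is dropped under both. Between 10% and 20%, 2.7.4 and 2.8.4 would drop it as a categorical variable while 2.4.4 would keep it. In either case the subgroup in 2.4.3 and 2.8.3 has no stated analysis.

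**The case against.** **One workable rule exists.** Section 2.8.4 gives both limits in one paragraph, 20% in general and 10% for categorical variables, and 2.7.4 presents its rules as tiered. On this view only 2.4.4 is out of line. That narrows the repair, but the conflict stands: 2.4.4 applies 20% and MICE to all variables, so reading 20% as the continuous limit and 10% as the categorical limit does not reconcile the sections.

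**Odds ratios are not what the trial reports.** The model is a ResNet-50 network and the primary contrast is a difference in AUC between clinician groups. Imputed predictors reach that contrast mainly through the model's score. This stands. A reader might infer from the odds ratios that the primary result is seriously at risk, but shifts of about 0.01 to 0.03 in AUC are small against the planned difference of 0.15.

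**Safeguards exist.** The complete-case comparison in 2.8.5 would partly expose sensitivity to the mode fill. Mandatory entry fields (2.7.4) and the exclusion of patients with incomplete baseline data (2.2.2) reduce the amount imputed. These points stand in part: they limit the damage but do not say which rule applies, and entry fields cannot repair retrospective 2019 to 2024 records.

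**The vaccination subgroup is not shown to be lost.** A reader might conclude that the stricter categorical rule, or mode imputation, removes it. The documents do not support that. The example belongs to the 20% clause, no missingness rate is given, and the wording marks it only as an example. The loss is possible, not established.

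**Conclusion.** The concern holds in this form: section 2.4.4 contradicts 2.7.4 and 2.8.4 for every categorical variable with up to 20% missing, and the latter two leave exactly 10% undefined. This follows from the text alone and is certain.

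Mode filling is a poor method here, but its size should be stated with restraint. Bias in a predictor's association is modest if missingness is unrelated to outcome and larger, in either direction, if it is related. The effect on AUC is probably small. These sizes rest on assumed prevalences, effects and missingness rates, and on logistic models rather than the planned network.

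The vaccination subgroup may be lost if missingness exceeds whichever limit applies. That is a separate, conditional gap. The whole point is something the sponsor should correct; it does not by itself undermine the primary comparison.

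**What to change.** 1. State one rule, identically, in 2.4.4, 2.7.4 and 2.8.4: a single exclusion threshold for all variable types, with the boundary value assigned to one side.
2. Include categorical variables in the planned MICE, with logistic or polytomous models, in place of mode imputation. The AUC-variation check in 2.8.5 then covers categorical uncertainty too.
3. Use the outcome in the imputation model for model-development data only. For validation data and real-time scoring, impute predictors without the outcome, by a procedure fixed on the training data. Otherwise the outcome leaks into the validation AUC. In Phase V, where predictions are issued within 2 h of case entry, the outcome is not yet known.
4. Exempt pre-defined subgroup variables from the exclusion rule. Analyse vaccination status with imputation or with an explicit 'unknown' level, and say which.

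The cost is wording in three sections and a little more analysis work. No extra patients, data or software are needed, since MICE is already planned.

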#### Data storage and security

2.7.5

To safeguard participant confidentiality, all patient identifiers will be removed and replaced with unique, non-traceable study IDs. Anonymized data will be stored in encrypted formats on password-protected servers hosted through the OSF platform (osf.io/ayj75), a secure repository compliant with international data protection standards. Access to the dataset will be restricted to authorized researchers via two-factor authentication, ensuring that only verified personnel with explicit permissions can retrieve or modify the data. This multi-layered security framework aligns with General Data Protection Regulation (GDPR) and China’s Data Security Law, prioritizing privacy while enabling rigorous scientific analysis. Lidström et al. also advocate the idea of securing patient data (37).

### Statistical analysis

2.8

#### Primary outcome analysis

2.8.1

The AUC will serve as the primary metric to evaluate the diagnostic accuracy of the AI model. To account for variability inherent in multi-reader, multi-case study designs, the DBM method will be employed, which adjusts for differences in clinician interpretations and case complexity. Analyses will be conducted using the MRMCaov (v0.2.1) and pROC (v1.18.0) packages in R, generating AUC values with 95% confidence intervals (CIs) derived from non-parametric bootstrapping (1,000 iterations). A clinically significant improvement is predefined as a ΔAUC more than 0.15 between the model-assisted and control groups, with the null hypothesis assuming no discriminative capacity (AUC less than 0.70, equivalent to random guessing). This approach ensures robust statistical inference while addressing real-world diagnostic variability across clinicians and settings. Hyperparameter optimization was conducted via Bayesian optimization with 5-fold cross-validation, prioritizing AUC on the validation set.

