#### Phase IV: randomized controlled trial

2.3.4

This phase is a pragmatic randomised controlled design to assess the effectiveness of AI-assisted diagnosis in the real world. Clinicians will be assigned in a 1:1 ratio to either the control group (using standard clinical assessment protocols) or the AI model-assisted group. Allocation will be by block group randomisation, stratified by hospital level (urban vs. rural) and clinician experience level (resident, attending, chief) to ensure balanced representation in key subgroups.

The control group will rely exclusively on routine diagnostic workflows, while the model-assisted group will integrate AI outputs into their decision-making process and retain full authority to accept or reject recommendations. The primary outcome is the between-group AUC difference, with a ΔAUC greater than 0.15 defined as clinically significant, which is consistent with the U.S. Food and Drug Administration’s (FDA) benchmarks for diagnostic tools based on artificial intelligence or machine learning (AI/ML). The design simulates real-world clinical practice and quantifies the added value of AI in improving diagnostic accuracy while preserving clinician autonomy.

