#### Phase V: prospective validation study

2.3.5

As Dai et al. illustrate the point, using prospective cohort data validation provides a better view of the model’s performance in the real world (24). This final phase evaluates the model’s real-world clinical utility during the 2025 influenza season. The AI model will be deployed in real time to analyze EHRs of newly admitted influenza patients across all 87 hospitals. Clinicians will receive model-generated predictions (such as risk scores, key contributing factors) within 2 h of case entry via a secure, institution-specific dashboard.

Data collection will capture:

Clinician actions: Initial diagnosis (pre-model assessment), final diagnosis (post-model review), and time-to-decision (minutes from case entry to diagnosis).Model performance: Concordance between model predictions and ground truth (severe influenza confirmed by an independent adjudication panel).

This prospective design validates the model’s operational feasibility, diagnostic timeliness, and accuracy in dynamic clinical environments, providing critical evidence for scalability and regulatory approval.

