#### Primary outcome

2.4.1

As the ultimate goal of this clinical trial is to create highly accurate AI models. Therefore the primary outcome metric was set as the area under the curve (AUC) (25). The AUC quantifies the discriminatory ability of the AI model so that it can distinguish patients who may develop severe influenza from those who will not. Since calculating the AUC requires the use of sensitivity, specificity, true positive rate, true negative rate, false positive rate, and false negative rate, more details describing these results can be found in our separate studies (16, 20).

To account for differences in diagnostic assessments after multiple clinicians read the cases, we planned to use the Dorfman-Berbaum-Metz (DBM) method. The DBM adjusts for differences in diagnostic assessments by clinicians so that AUC difference values between the two groups can be estimated (22). ROC curves were calculated using the pROC (version 1.18.0) software package (28). The AUC values as well as their 95% confidence intervals will then be calculated using MRMCaov (version 0.2.1) (27). For differences between the experimental and control groups, we expected to use the Mann-Whitney U test (29). Clinically significant improvement was defined as an AUC difference between the experimental and control groups greater than 0.15. The null hypothesis here is that the AUC difference is less than 0.7, and the AI model has no discriminatory power. Our method of using AUC to set thresholds not only follows statistical patterns, but is also highly compliant with the criteria for the development of AI-driven diagnostic tools.

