#### Sample size derivation

2.5.2

The sample size calculation began with an initial estimate of 145 patients per group (290 total), derived from a power analysis targeting a clinically significant ΔAUC of 0.15 (*α* = 0.05, *β* = 0.95). To account for potential 20% attrition due to incomplete data or participant dropout, the final patient sample was adjusted to 174 per group (348 total). For clinicians, a minimum of 218 participants (109 per group) was required to ensure balanced representation across experience levels (resident, attending, chief) while addressing hospital-level clustering effects, as recommended by methodology for cluster-randomized trials (35). This dual-tiered approach balances statistical precision with pragmatic considerations, ensuring robust evaluation of the AI model’s impact in diverse clinical environments.

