#### Secondary outcomes analysis

2.8.2

Secondary endpoints include diagnostic sensitivity and specificity, calculated using the Clopper-Pearson exact method for binomial proportions to determine the model’s and clinicians’ ability to correctly identify true positive and true negative cases, respectively. Differences between clinician and model performance will be assessed via the Mann–Whitney U test, a non-parametric method suitable for skewed distributions. Positive and negative predictive values (PPV/NPV) will be adjusted for influenza prevalence using Bayes’ theorem and reported with 95% confidence intervals to reflect their clinical utility in real-world settings. The misdiagnosis rate, defined as the sum of false positives and false negatives per 100 diagnoses, will be analyzed using an independent samples t-test (if normally distributed) or Wilcoxon rank-sum test (for non-normal data), quantifying the model’s impact on reducing diagnostic errors. These metrics collectively evaluate the model’s precision, reliability, and practical value in augmenting clinical decision-making.

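### The DBM method and the Mann-Whitney U test named for the between-group AUC difference do not fit Phase IV, where each clinician works in one arm with that arm's own patients

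*Protocol article*

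**What the plan says.** All references are to the protocol article.

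- **Method for the primary outcome.** Section 2.8.1 states: "To account for variability inherent in multi-reader, multi-case study designs, the DBM method will be employed". The same paragraph sets the 0.15 threshold for the model-assisted versus control contrast. Section 2.4.1 gives the purpose: "The DBM adjusts for differences in diagnostic assessments by clinicians so that AUC difference values between the two groups can be estimated".
- **Where that contrast is primary.** Section 2.3.4 (Phase IV): "The primary outcome is the between-group AUC difference, with a ΔAUC greater than 0.15 defined as clinically significant".
- **Phase IV layout.** "Clinicians will be assigned in a 1:1 ratio to either the control group (using standard clinical assessment protocols) or the AI model-assisted group". Section 2.6.3 describes control patients as receiving usual care that rests on their own clinicians' judgement.
- **Numbers.** Section 2.5.2 gives 174 patients per group (348 in all) and, for clinicians, "a minimum of 218 participants (109 per group) was required". Section 2.5.3 spreads the 348 patients over retrospective and prospective cohorts.
- **Between-group test.** Section 2.4.1 also says: "For differences between the experimental and control groups, we expected to use the Mann-Whitney U test".
- **Secondary outcomes.** Section 2.8.2, on sensitivity and specificity: "Differences between clinician and model performance will be assessed via the Mann–Whitney U test".
- **Phase III, for contrast.** Section 2.3.3 has every clinician assess cases in two rounds, without and then with the model, with the cases reordered between rounds.

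**The concern.** DBM analyses pseudovalues of each reader's own AUC. In its usual form, the same readers assess the same cases under both conditions. Phase III has that layout. In Phase IV a clinician is in one arm only and patients belong to that arm, so readers and cases are both nested in arm.

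A Mann-Whitney comparison between arms asks whether scores in one arm tend to be higher than in the other. The Phase IV question is different: whether severe and non-severe patients are better separated in one arm.

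At stake is the primary result of the only randomised phase. One named method does not match the design. The other can miss the effect the trial is sized for, or report a difference when discrimination is the same. The second error is plausible here, because showing clinicians a risk score could move their ratings up or down without improving discrimination.

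**Working it through.** **1. The plan's own figures.** 145 × 1.2 = 174 patients per group, and 2 × 174 = 348. For clinicians, 2 × 109 = 218. These totals agree with each other. The 145 itself does not follow from the printed formula: (1.96 + 1.645)² × (0.85 × 0.15 + 0.70 × 0.30) / 0.15² = 12.996 × 0.3375 / 0.0225 = 194.9. That is a separate matter, and nothing below depends on it.

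**2. Patients per clinician.** The article does not state this ratio. Assume that all 348 patients enter Phase IV and that one clinician assesses each. Then 348/218 = 174/109 = 1.60. On the 290 patients before the attrition allowance it is 290/218 = 1.33.

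**3. Clinicians with any AUC.** A clinician's AUC needs at least one severe and one non-severe patient. Spread as evenly as possible, 174 patients over 109 clinicians gives 65 clinicians with two patients and 44 with one (65 × 2 + 44 = 174). With severe share p, a clinician with two patients sees both classes with probability 2p(1 − p). The article gives no severe share, so p is an assumed range. The second and third results allocate patients to clinicians at random (2,000 simulated allocations). Leave-one-out AUCs, which DBM pseudovalues use, need two patients of each class.

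| Severe share p | Even spread: 65 × 2p(1 − p) | Random spread: both classes seen | Random spread: two of each class |
|---|---|---|---|
| 5% | 6.2 | 6.5 | 0.1 |
| 10% | 11.7 | 12.2 | 0.5 |
| 20% | 20.8 | 21.5 | 1.6 |
| 30% | 27.3 | 28.0 | 2.7 |
| 50% | 32.5 | 33.0 | 3.9 |

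Entries are expected numbers out of 109 clinicians per arm. So about 6 to 33 (6% to 30%) would have an AUC at all, and at most about 4 would support leave-one-out. Under the even spread nobody has four patients, so none would.

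**4. What Mann-Whitney tests.** Within one arm, U divided by (number severe × number non-severe) is that arm's AUC. Between arms, the test asks whether a score from one arm is equally likely to lie above or below a score from the other, whatever the patients' true status. A simulation used two arms of 174, normal scores within each class, 2,000 runs per setting and a two-sided 5% level:

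| Assumed severe share | AUC 0.85 vs 0.70, scores with equal mean and SD: rejected | AUC 0.70 vs 0.70, one arm shifted by 0.5 within-class SD: rejected |
|---|---|---|
| 10% | 5.1% | 99.1% |
| 30% | 5.5% | 99.1% |
| 50% | 5.5% | 99.4% |

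The test has almost no power beyond its nominal level for the effect the trial seeks, and it rejects nearly always when the AUCs are equal but ratings are shifted. Applied instead to clinicians' own AUCs, it could compare arms, but step 3 shows how few clinicians would supply one.

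**5. Section 2.8.2.** Where the model and the clinician judge the same patients, as in Phase V, each patient gives a pair of correct/incorrect results. An unpaired rank test ignores that pairing.

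**The case against.** The strongest defence is that section 2.8.1 justifies DBM by reference to multi-reader, multi-case designs, which is the title of Phase III, where the method fits. But sections 2.4.1 and 2.8.1 attach it to the contrast between the model-assisted and control groups. If DBM is read as meant for Phase III only, Phase IV is left with Mann-Whitney as its only named between-group test, which step 4 rules out.

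Several stronger readings are tempting, and the documents do not support them.

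- **That DBM cannot be run in any form.** Having each clinician in one arm rules out the crossed form only. Nested forms exist, and their obstacle is cases per clinician.
- **That 1.6 patients per clinician is a design fact.** It is derived. Section 2.5.3 suggests that fewer than 348 patients belong to Phase IV, which would lower the ratio. Only several clinicians per patient would raise it; the article does not say this, and the usual-care description does not suggest it.
- **That clinicians give only a yes/no diagnosis, so their ROC curve has one point.** The form of the Phase IV response is not stated, and Phase III records confidence on a 5-point scale.
- **That Mann-Whitney is a fallback and the bootstrap a rival test, with the choice left until the data are seen.** Section 2.4.1 lists Mann-Whitney beside DBM, and section 2.8.1 uses the bootstrap only for confidence intervals. The resampling unit can properly be left to an analysis plan.

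Pairing in section 2.8.2 is also partly inferred, since that section does not name the phase or the data layout. The point there is limited to cases that both model and clinician judge.

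**Conclusion.** Wrong as written. This is a mismatch between the named methods and the Phase IV design, not detail that a condensed article may leave out. Two parts of the conclusion need no assumed figures: the crossed form of DBM does not fit clinicians and patients nested in arm, and a between-arm Mann-Whitney test does not test whether two AUCs are equal. The simulated rejection rates illustrate the second part and depend on normal scores and the chosen shift.

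The size of the difficulty for nested multi-reader forms does rest on assumptions: all 348 patients in Phase IV, one clinician per patient, and a severe share of 5% to 50%. Within that range at least 70% of clinicians per arm would have no AUC. No corrected sample size can be given, because between-clinician variance, within-clinician correlation and the severe share are not stated.

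**What to change.** 1. In sections 2.4.1 and 2.8.1, limit DBM and MRMCaov to Phase III.
2. For Phase IV, name one primary analysis: the difference between the two arms' independent empirical AUCs, with a 95% confidence interval that allows for clustering by clinician. The 1,000-iteration bootstrap already in section 2.8.1 can serve if it resamples clinicians with all their patients, within arm and randomisation stratum.
3. Remove Mann-Whitney as the between-group test in section 2.4.1.
4. In section 2.8.2, where model and clinician judge the same cases (for example in Phase V), compare sensitivity and specificity with a paired binary method that also allows for clustering by clinician, such as GEE.

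The edits cost wording only. The downside is that the interval may be wider than one that ignores clustering. Whether the planned numbers then suffice cannot be settled from the article, so the sponsor should check the sample size on the same basis as the chosen analysis and state how many patients belong to Phase IV.
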